# A pilot randomized trial of conventional versus advanced pelvic floor exercises to treat urinary incontinence after radical prostatectomy: a study protocol

**DOI:** 10.1186/s12894-015-0088-4

**Published:** 2015-09-16

## Abstract

**Background:**

Radical prostatectomy is the most common and effective treatment for localized prostate cancer. Unfortunately, radical prostatectomy is associated with urinary incontinence and has a significant negative impact on quality of life. Pelvic floor exercises are the most common non-invasive management strategy for urinary incontinence following radical prostatectomy; however, studies provide inconsistent findings regarding their efficacy. One potential reason for sub-optimal efficacy of these interventions is the under-utilization of regional muscles that normally co-activate with the pelvic floor, such as the transverse abdominis, rectus abdominis, and the diaphragm. Two novel approaches to improve urinary continence recovery are ‘Pfilates’ and ‘Hypopressives’ that combine traditional pelvic floor exercises with the activation of additional supportive muscles. Our study will compare an advanced pelvic floor exercise training program that includes Pfilates and Hypopressives, to a conventional pelvic floor exercises regimen for the treatment of post-radical prostatectomy urinary incontinence.

**Methods/Design:**

This is a pilot, randomized controlled trial of advanced pelvic floor muscle training versus conventional pelvic floor exercises for men with localized prostate cancer undergoing radical prostatectomy. Eighty-eight men who will be undergoing radical prostatectomy at hospitals in Toronto, Canada will be recruited. Eligible participants must not have undergone androgen deprivation therapy and/or radiation therapy. Participants will be randomized 1:1 to receive 26 weeks of the advanced or conventional pelvic floor exercise programs. Each program will be progressive and have comparable exercise volume. The primary outcomes are related to feasibility for a large, adequately powered randomized controlled trial to determine efficacy for the treatment of urinary incontinence. Feasibility will be assessed via recruitment success, participant retention, outcome capture, intervention adherence, and prevalence of adverse events. Secondary outcomes of intervention efficacy include measures of pelvic floor strength, urinary incontinence, erectile function, and quality of life. Secondary outcome measures will be collected prior to surgery (baseline), and at 2, 6, 12, 26-weeks post-operatively.

**Discussion:**

Pfilates and Hypopressives are novel approaches to optimizing urinary function after radical prostatectomy. This trial will provide the foundation of data for future, large-scale trials to definitively describe the effect of these advanced pelvic floor exercise modalities compared to conventional pelvic floor exercise regimes for men with prostate cancer undergoing radical prostatectomy

**Trial registration:**

Clinicalstrials.gov Identifier: NCT02233608.

## Background

Radical prostatectomy (RP) is the most common treatment for localized prostate cancer (PCa) [1, 2] with a >90 % 15-year disease-specific survival for men with localized disease [3]. Unfortunately, RP is associated with post-operative urinary incontinence (UI) that can persist for two years or longer and is related to significant reductions in overall health-related quality of life (QoL) [4–7]. Moreover, UI can be an important economic burden to patients due to the cost of pads and lost work productivity [8]. Given the prevalence of RP in the management of PCa and the associated psychosocial, functional, and economic adversity caused by UI, expediting the recovery of urinary control is a major priority for patients and their clinicians.

**Fig. 1 Fig1:**
[figure not shown]
Participant Flow

Normally, the pelvic floor muscles (comprised of the internal sphincter, levator ani, coccygeus, striated urogenital sphincter, external anal sphincter, ischiocavernosus, and bulbospongiousus) work in a coordinated fashion to promote urinary control [9, 10]. While the exact etiology of post-RP UI is not well understood, it is hypothesized to result from injury to the internal sphincter and/or an onset of bladder detrusor hyperactivity that can cause urge incontinence through pressure on the bladder walls [10–16]. Consequently, continence becomes dependent on the pelvic floor musculature that supports the *external* urethral sphincter [12, 17, 18], and thus voluntary conditioning of these muscles is considered a primary, non-invasive UI management strategy post-RP [19, 20].

Conventional pelvic floor muscle exercises (PFMX) are intended to improve urinary control by increasing the strength, endurance, and coordination of the pelvic floor muscles and functional activation of the external urethral sphincter [21–23]. Moreover, chronic performance of PFMXs is suggested to cause hypertrophy of the periurethral striated muscles, a resultant stiffening and strengthening of the pelvic floor muscles and connective tissues, and an inhibition reflex of the detrusor muscles [24–26]. Collectively, the PFMXs facilitate improved capability for external urethral constriction [9] and relaxed detrusor activity to aid in the recovery of post-RP UI [27, 28]. PFMXs typically involve instructions to ‘lift up’ the pelvic floor to stop the flow of urine [17, 21, 29]. PFMX training starts with pelvic floor muscle identification through biofeedback, typically through active urinary flow control (i.e. voluntarily starting and stopping urination) and cueing (using imagery to identify and activate the correct muscles). Once appropriate control is observed, patients are instructed to practice the same contractions routinely with a target volume, intensity, frequency, and/or duration [23].

A recent Cochrane review on the management of UI after RP found a small to moderate benefit of conventional PFMXs; however, none of the included studies incorporated training of the surrounding muscles [21]. The paucity of evidence and modest benefits related to the management of UI with the engagement of surrounding muscle to the pelvic floor is salient because of the growing literature demonstrating that pelvic floor muscle contraction is optimized with co-activation of the abdominals and other regional muscles [30–34]. In particular, the transverse abdominis (TrA), rectus abdominis, and diaphragm muscles are often neglected in PMFX approaches despite their requirement for optimal pelvic floor activation [30, 33]. The relationship between the TrA and diaphragm with pelvic floor activation is described in several lines of research. First, Neumann et al. [33] observed that relaxation of the abdominal wall during pelvic floor muscle contraction only elicits 25 % of the maximal voluntary contraction of the pelvic floor. Second, research has indicated that the likelihood of poor pelvic floor tonic activity (autonomic contraction), and consequent risk of UI, is apparent when the ability of the TrA to maintain a contraction is impaired [30–32]. Third, improved tonic activity of the pelvic floor may improve the autonomic urethral constriction that could prevent leakage without conscious intervention [35, 36]. Similarly, ‘deep belly’ breathing exercises that emphasize diaphragmatic contraction and relaxation have been shown to improve pelvic floor muscle activation and reduce intra-abdominal pressure in women with incontinence [30, 37, 38].

More recent PFMX paradigms incorporate techniques aimed at optimizing pelvic floor muscle responsiveness and contraction quality through the utilization of other regional muscles. One such approach is “Pfilates” (‘*P*elvic *F*loor P*ilates*’) that incorporates the fundamental elements of Pilates (a form of exercise that focuses on core strength, stability, flexibility, and muscle control, as well as posture and breathing) [39, 40] with targeted pelvic floor activation [41]. Pfilates includes several static poses that activate the TrA, hip adductors, gluteal, and pelvic floor muscles with instructions to pulse (small range of motion) with short, maximal effort contractions of the engaged muscles. A recent study by Culligan et al. [40] demonstrated comparable improvements in pelvic floor strength measured by perineometry after 12 weeks of conventional PFMX versus Pilates in 62 women with little or no pelvic floor muscle dysfunction. Although UI was not measured, this study suggests that Pilates may produce similar benefits for UI as traditional PFMXs.

Another novel approach to PFMXs is known as ‘Hypopressive’ exercises. Hypopressive exercises emphasize engaging the TrA with conscious coordination of the diaphragm with breathing that is hypothesized to increase muscle tone of the pelvic floor muscles and subsequently cause urethral constriction [30, 42–45]. While executing the prescribed Hypopressive techniques, the use of deep breathing followed by a brief breath-hold causes relaxation of the diaphragm, decrease in intra-abdominal pressure, and a reflex contraction of the pelvic floor muscles, unconsciously maximizing a contraction and consequently improving re-conditioning of these muscles [43, 45]. Caufriez [46] communicated this technique in 1997 and described the steps as follows: slow diaphragmatic inspiration, followed by total expiration and, after glottal closure, a gradual contraction of the abdominal wall muscles, with superior displacement of the diaphragm cupola (referred to as diaphragmatic aspiration). There is significant attention drawn to the distension of the ribs, breathing, and body positions, so that even though one is aware of their pelvic floor, it is an unconscious movement [30, 38, 43]. Early research on the effects of Hypopressive exercise programs have demonstrated increased tonic activity, strength, and size of the pelvic floor muscles via ultrasonography imaging [44].

To date, no study has assessed the effect of a comprehensive PFMX regimen that includes Pfilates and Hypopressives for UI. This represents a major gap in our understanding of non-invasive UI management strategies for PCa patients especially since the benefits of PFMX are modest and emerging literature suggests that the pelvic floor muscles are suboptimally activated during more focused pelvic floor training.

## Methods

This study is a 2-arm, pilot randomized controlled trial (RCT) that compares the effect of a conventional PFMX program, considered usual care (UC), to an advanced pelvic floor exercise program (APFX) including Pfilates, and Hypopressive for the management of UI after RP for PCa. The primary objective of this study is to assess the feasibility of conducting a full-scale RCT of similar design. Feasibility will be determined via recruitment success, participant retention, outcome capture, intervention adherence, and prevalence of adverse events. Our secondary objectives are to compare the efficacy of APFX to UC in UI, pelvic floor strength, erectile function, and QoL after RP. This study will be conducted at the Wellness and Exercise for Cancer Survivors (WE-Can) program at the Princess Margaret Cancer Centre. WE-Can is a multidisciplinary team of physicians, physiotherapists, kinesiologists, and other exercise professionals that provide exercise and physical activity programming for cancer survivors.

This study has been approved by the ethics boards of the participating institutions and all participants will be asked to provide voluntary and informed consent.

### Study population/participants

Eighty-eight participants will be recruited for this trial. We anticipate an attrition rate of 20 % by the 26-week follow-up assessment to yield 70 participants (35 participants per group) for main efficacy estimate analyses that is aligned with recommended pilot and feasibility study sample sizes for treatment effect estimates [47–49]. *Inclusion Criteria*: Patients that: i) have localized PCa who have consented for RP (open retropubic, laparoscopic, or robot-assisted laparoscopic); ii) are between the ages of 40 and 80 years; and iii) are proficient in English. *Exclusion Criteria*: Patients that: i) are diagnosed with a known neurological disease, autoimmune connective tissue disorder; ii) have prior experience with pelvic floor training by a healthcare provider; iii) have uncontrolled hypertension; iv) have diagnosed chronic obstructive pulmonary disease (COPD) and/or chronic restrictive respiratory disease; v) have a history of inguinal herniation; or vi) have hypertonic pelvic floor muscles upon baseline evaluation. Pelvic floor tonicity will be assessed by a specially trained pelvic floor physiotherapist via digital rectal examination. Hypertonic pelvic floor is determined by the physical examination findings of extrapelvic musculoskeletal and connective tissue examination, as well as the elements of patient history [50]. These patients who exhibit levator ani hypertonicity (tension myalgia) will be excluded as they can experience pelvic, urogenital, and rectal pain; tightness and spasticity; and adverse effects on sexual, urinary, and bowel function that may be exacerbated with contraction-based pelvic floor training [51, 52].

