### Study recruitment and randomization

Recruitment will occur in the Greater Toronto Area (total population 4.5 million) in urological oncology clinics and through presentations and/or information stands [52] set-up at local PCa support group meetings. These peer-support meetings often include men who have been recently diagnosed and are considering various treatments for PCa, including RP. Men who self-identify as eligible will receive further verbal and written information about the study. Those deemed eligible and are interested will be asked to provide written consent.

Participants will be 1:1 randomized to the UC and APFX groups, stratified by age (±60 years). Blinded allocation of the participants to their treatment groups will be performed via a process consisting of placing the intervention assignments into opaque envelopes, sealing and shuffling the envelopes, and sequentially numbering them with each new participant receiving an envelope in sequence of recruitment. The envelopes will be opened by the research coordinator with the participant following the baseline assessment, prior to RP Fig. 1.

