## Outcome measures

Participants will complete five study assessments: baseline (approximately 1 week prior to RP), and at 2, 6, 12, 26-weeks post-operatively. Each assessment session will take place in Toronto, Ontario at the Princess Margaret Cancer Centre in the WE-Can Program. Participant demographics and self-reported disease and treatment-related variables will be collected at the baseline assessment.

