## Statistical analysis

Participant characteristics at baseline will be compared using independent sample t-tests or chi-square tests. We will report retention and compliance rates for the sample and their associated 95 % CI as well as reasons for non-participation of eligible patients. To calculate outcome capture, we will calculate the proportion of participants who have complete data on each outcome at each time point divided by the total number of study participants. Estimates of efficacy (Group and Time main effect, as well as Group x Time interactions) will be analyzed using a repeated-measure analysis of covariance (ANCOVA), controlling for the baseline value of the outcome of interest. We will examine the effect size (Cohen’s d) of the intervention on the clinical outcomes by dividing the observed mean between-group difference in change in the outcome measure from baseline to follow-up (UC vs. APFX) by its standard deviation.

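### The number, model and effect size given for efficacy fit a complete-case analysis, which could leave about 18 of 88 randomised men unused; a mixed model on all available visits should be named instead

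*Protocol article*

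**What the plan says.** Under Study population/participants, the protocol article gives the recruitment target ("Eighty-eight participants will be recruited for this trial"), the expected loss ("We anticipate an attrition rate of 20 % by the 26-week follow-up assessment") and the result: "to yield 70 participants (35 participants per group) for main efficacy estimate analyses". The same sentence supports that number by reference to recommended pilot sample sizes for estimating treatment effects. It gives no power calculation.

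Under Study recruitment and randomization: "Participants will be 1:1 randomized to the UC and APFX groups, stratified by age". The envelope is opened "following the baseline assessment, prior to RP", so every man counted in the 88 is randomised before surgery and before any follow-up.

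Under Outcome measures: "Participants will complete five study assessments: baseline (approximately 1 week prior to RP), and at 2, 6, 12, 26-weeks post-operatively". Pelvic floor strength is the exception, with no week-2 measurement.

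Under Statistical analysis, group, time and group-by-time effects "will be analyzed using a repeated-measure analysis of covariance (ANCOVA), controlling for the baseline value of the outcome of interest". The effect size is obtained by "dividing the observed mean between-group difference in change in the outcome measure from baseline to follow-up (UC vs. APFX) by its standard deviation". The age stratum is not named in the model. The same section computes outcome capture, a feasibility measure, with all study participants as the denominator; the efficacy sentences carry no such wording.

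Feasibility is the primary objective (Methods) and efficacy is secondary.

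**The concern.** Three statements about efficacy point the same way. The number quoted for the analysis is the number still present at week 26. The named model, in its classical form, drops any man with a missing post-operative value. The effect size is built on observed change, which at week 26 exists only for men seen at week 26.

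A man who attends weeks 2, 6 and 12 and then leaves would add nothing to the classical ANCOVA or to a week-26 d. If the reasons for leaving are related to outcome, and differ between a multi-component programme and usual care, the men left in each arm are no longer comparable in the way randomisation made them. The article presents the trial as the data foundation for larger trials, so a distorted or needlessly imprecise effect estimate could carry over into their planning.

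**Working it through.** **1. The plan's own figure.** Inputs from Study population/participants: 88 recruited, 20% attrition, 70 at week 26.
- Forward: 88 × (1 − 0.20) = 70.4, i.e. 70, or 35 per arm.
- Backward: 70 / 0.80 = 87.5, rounded up to 88; per arm 35 / 0.80 = 43.75, rounded up to 44.

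The figure reproduces. Outside the 70 are 88 − 70 = 18 men, and 18/88 = 20.5%.

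**2. Visits that could go unused.** Inputs from Outcome measures: four post-operative visits (weeks 2, 6, 12, 26).
- Scheduled: 88 × 4 = 352.
- Earlier visits of men lost only at week 26: at most 18 × 3 = 54, and 54/352 = 15%.
- Pelvic floor strength (weeks 6, 12, 26): at most 18 × 2 = 36, of 88 × 3 = 264.

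These are maxima. They assume that each of the 18 attended every visit before week 26.

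**3. Precision.** For a standardised difference with n men per arm, SE = √(2/n) and the 95% half-width is 1.96 × SE. This is a normal approximation without the gain from baseline adjustment.

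| Men analysed | n per arm | SE | 95% half-width |
|---|---|---|---|
| 70 | 35 | √(2/35) = 0.239 | 0.47 SD |
| 88 | 44 | √(2/44) = 0.213 | 0.42 SD |

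The second row is a best case. A man without week-26 data carries only partial information about week 26, and a man with no post-operative visit carries almost none.

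**4. Bias, by assumption.** The document gives nothing from which bias can be computed. Suppose a proportion p = 18/88 is lost in each arm. Within an arm, the completer mean differs from the full-arm mean by p × (completer mean − dropout mean). If that gap differs between arms by g, the completer contrast shifts by p × g:
- g = 0: shift 0
- g = 0.25 SD: 0.2045 × 0.25 = 0.05 SD
- g = 0.5 SD: 0.2045 × 0.5 = 0.10 SD
- g = 1.0 SD: 0.2045 × 1.0 = 0.20 SD

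A severe case gives a similar upper end. Suppose one arm loses exactly its worst 20% at week 6 and loss in the other arm is non-selective. The selected arm's week-6 mean shifts by φ(0.8416)/0.8 = 0.35 SD. With an assumed within-man correlation of 0.4 to 0.6, the week-26 shift is 0.35 × 0.4 = 0.14 to 0.35 × 0.6 = 0.21 SD. Here dropout depends on a recorded week-6 value, which is the kind of dropout a likelihood-based model using week 6 can handle and a complete-case analysis cannot.

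**The case against.** The strongest reply is that the article never defines a completer set. The sentence giving 70 is an attrition allowance in a sample-size paragraph, and planning for 70 evaluable men does not exclude the other 18. A repeated-measures ANCOVA can also be fitted as a mixed model that uses every available visit. Analysis sets and missing-data rules are commonly left to a full protocol or SAP, which is not shown here. All of this stands, and the absence of a missing-data rule is not the complaint. The point concerns what is stated: a week-26 number for efficacy, a model whose classical form needs complete data, and an effect size on observed change. Fitting the ANCOVA as a mixed model would still leave the week-26 d, as worded, resting on men observed at week 26.

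Two stronger readings are tempting, and the document supports neither:
- *That the 18 men and their earlier visits are discarded, so the comparison is no longer between randomised groups.* No sentence excludes them, and nothing moves men between arms or selects them by adherence. Bias depends on the dropout pattern and is zero if loss is balanced and equally selective in both arms.
- *That even 70 is unattainable unless no retained man misses a visit.* Assuming 5% missed at each of weeks 2, 6 and 12, 70.4 × 0.95³ = 60.4 complete cases (66.3 at 2%, 51.3 at 10%). These rates are not in the document. The calculation does not apply to a baseline-to-week-26 d, which needs two measurements. For pelvic floor strength, with no week-2 visit, it becomes 70.4 × 0.95² = 63.5.

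It is also fair to say that the feasibility outcomes do not depend on this model, and that outcome capture by visit will make missing data visible.

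**Conclusion.** The point holds as a risk built into the stated combination of number, model and effect size. It is not an exclusion that the plan announces. If the methods are applied in their classical form and attrition is as planned, about 18 of 88 men and up to 54 of 352 scheduled post-operative visits go unused. The loss of precision is modest: a half-width of 0.47 SD, against 0.42 SD at best. The possible bias at week 26 runs from 0 to about 0.2 SD. That range rests wholly on assumed dropout patterns, and its upper end needs strongly selective loss that differs between arms.

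Severity is moderate. Efficacy is secondary in this pilot, but the sample size is justified by treatment-effect estimation and the remedy is cheap.

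**What to change.** In Statistical analysis, replace the repeated-measures ANCOVA with a likelihood-based mixed model for repeated measures:
- all randomised men analysed in the arm to which they were randomised, with all available post-operative visits;
- terms for arm, visit, arm-by-visit, the baseline value of the outcome, and the age stratum used in randomisation;
- the standardised effect at each visit taken from the model's arm contrast, with the standard deviation used as divisor stated, in place of raw observed change.

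In Study population/participants, describe 70 as the number expected to complete week 26, not as the set analysed. Keep the completer analysis as a sensitivity analysis.

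The cost is a few sentences, slightly more analysis work in standard software, and reliance on a missing-at-random assumption. The model does not remove bias if dropout depends on outcomes that were never recorded, so the reasons for and timing of dropout should be reported by arm alongside it. No extra participants, visits or measurements are needed.
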